### Intervention

#### Usual care

This will be NHS treatment as usual (TAU). Participant dyads randomised to this group will receive standard NHS care delivered by their department, for example, physiotherapy, rheumatology, orthopaedic, occupational therapy or pain management services. This consists of patient-focused treatments which may include exercise, medication prescription and advice/education.^11–14^ This may be face-to-face or through video consultation approaches depending on the local NHS service provision. There is no routine ‘training’ element or hands-on skills or formal support for caregivers. Patients and their caregivers will not receive the JOINT SUPPORT programme or any caregiver training.

Treatment logs will be used to record the components of standard care. This will be completed by the clinical team to determine what interventions are received by the patient while they are under the care of that service.

#### Experimental intervention

The JOINT SUPPORT programme was developed from the evidence-base^9^ and following patient, caregiver and stakeholder input. The programme is developed and informed by Social Cognitive Theory.^20^ This is an explanation for behaviour in which individual learning happens in a social context, where people can put vicarious learning into practice, and learn together and from each other in the process. The three goals of the intervention are outlined below using a CONTEXT**–**MECHANISM**–**OUTCOME framework (figure 2)^21^ and logic model (figure 3).

**Figure 2 F2:**
[figure not shown]
Figure illustrating the CONTEXT–MECHANISM–OUTCOME framework for the JOINT SUPPORT intervention. MSK, musculoskeletal.

**Figure 3 F3:**
[figure not shown]
Figure illustrating the JOINT SUPPORT intervention logic model. ADLs, activities of daily living.

#### To improve caregiver knowledge, capability and skills by identifying and practising individualised chronic pain management strategies and physical activity participation in outpatient (or video consultation) settings that can be used for people with MSK pain

Caregivers of people with chronic musculoskeletal pain (CONTEXT) need the skills, capability opportunity and knowledge (MECHANISM) to be able to support and guide behaviour change for both patients and caregivers to increase health-related quality of life (HRQoL), reduce social isolation and improve self-management outcomes for patients (OUTCOME).

#### To reduce caregiver fear of movement and isolation when providing care for people with chronic pain

Chronic musculoskeletal pain leads to fear of movement, isolation and a loss of identity for caregivers (CONTEXT) requiring a re-evaluation of their role and identity (MECHANISM) to be able to support people with chronic musculoskeletal pain and promote good caregiver health and well-being (OUTCOME).

#### Support patients and caregivers to increase capability, set targets and monitor goals to facilitate patients improved symptom management

Patients with chronic musculoskeletal pain in an outpatient setting (CONTEXT) will be supported by caregivers to set personalised shared goals which they can realistically meet (MECHANISM) to facilitate improved functional, health-related outcomes and increased independence (OUTCOME).

Participants randomised to the JOINT SUPPORT programme will receive usual NHS treatment (control group intervention as detailed below) PLUS five, 1-hour, group-based training sessions, delivered by a study-trained physiotherapist or occupational therapist. The intervention will be delivered through two possible approaches.

Approach 1: Face-to-face delivery which will be group-based, consisting of a target of three to five dyads in each class. They will be delivered in an outpatient setting provided to both participants in the dyad by a study-trained physiotherapist or occupational therapist.

Approach 2: Video consultation if face-to-face consultations are not permitted within a participating NHS organisation, group-based video consultation sessions using an NHS authorised platform will be used to deliver the content of the JOINT SUPPORT programme as per the face-to-face delivery approach.

If there is a change in service delivery once a participant-dyad has started their JOINT SUPPORT programme, switching from Approach 1 to Approach 2 will be permitted, with the effects explored in the qualitative substudy.

#### JOINT SUPPORT training programme

The first session will aim to start within 6 weeks from consent. Sessions will be provided to both patient and caregiver participants by either a physiotherapist or occupational therapist. Irrespective of delivery method, each session will be up to 60 min. Throughout the five sessions, the JOINT SUPPORT healthcare professional will monitor the patient–caregiver competencies, providing continual feedback and critique to support the training. There will be a cognitive-behavioural approach used throughout the sessions, underpinned by social cognitive theory where dyads will be facilitated by a JOINT SUPPORT healthcare professional on the following topics:

##### Session 1

Understanding pain, caregiving and how pain affects the caregiving dyad.Introduction and explanation of the JOINT SUPPORT Workbook, highlighting material on pain and effects on the dyad.

##### Session 2

Pacing and graded activity.Goal setting.JOINT SUPPORT Workbook—highlighting material on goal-setting and problem-solving.

##### Session 3

Benefits of physical activity (reducing deconditioning, healthy ageing, physical and psychological health).Fear avoidance.JOINT SUPPORT Workbook—highlighting material on physical activity and fear avoidance.

##### Session 4

Medication use and management.JOINT SUPPORT Workbook—highlighting material on medication use and management.

##### Session 5

Working through case-study scenarios to re-enforce knowledge and critique competencies on JOINT SUPPORT skills.JOINT SUPPORT Workbook—highlighting material on case-scenarios and long-term goal setting.Confirmation of dates for JOINT SUPPORT telephone booster calls.

#### JOINT SUPPORT telephone booster calls

Following the five group-sessions, a JOINT SUPPORT healthcare professional will telephone each caregiver and patient as a dyad during Week 1, 3 and 6 post-group session discharge. Each call is expected to take approximately 20 min. Both the caregiver and patient participant should be in the same room during these calls. Topics covered in each call will include:

Recovery progress and current status based on patient–caregiver shared goals.Discussion on JOINT SUPPORT Workbook use and progress including goal-setting sheets.Support to create collaborative goals and positive reinforcement for continued recovery.

#### JOINT SUPPORT healthcare professional training

Designated healthcare professionals delivering the experimental intervention will attend a 1-day face-to-face course where, at the local participating site, they will be taught the JOINT SUPPORT intervention by a member of the research team. In addition, to assess the fidelity to the experimental intervention, the trial team will undertake a debriefing telephone/video call with a healthcare professional after they have delivered their first JOINT SUPPORT session.

#### Contamination

Participants will only receive their allocated intervention. During follow-up, participants may require further interventions as part of their recovery as per routine NHS practice. Further clinical interventions will be permitted for participants without having to withdraw from the trial, but these will be recorded by the central trial team. To assess the risk of crossover between groups, we will closely monitor case report forms (CRFs) and data pertaining to intervention delivery.

#### Co-interventions

This is a pragmatic study and patient–caregiver dyads in either group will not be asked to desist from receiving other forms of treatment during the study such as continuing rehabilitation, general practitioner consultations, medication changes or alternative treatments as required. Use of these treatments will be recorded through CRFs.

#### Quality assessment

The trial will be monitored and audited in accordance with the current approved protocol, principles of GCP,^19^ relevant regulations and standard operating procedures.

A quality control programme will be adopted to ensure protocol and intervention fidelity. We will collect data on what components of the interventions (control and experimental) were delivered. This is in respect of intervention parameters including: content, mode of delivery, staff delivered, frequency, timing of delivery and variation/deviations from the protocol. These will be collected through intervention logs and relevant CRFs. Quality assurance (QA) checks through site visits will be conducted at Month 1 from first randomisation (±3 weeks for each) at each site. These visits may be in-person or virtual. If there are concerns in relation to any aspect of the site visit, repeat visits with training may be undertaken to improve protocol compliance.

### Assessment

The data collection schedule is summarised in table 1.

**Table 1 T1:** Participant timeline illustrating schedule of enrolment, interventions and assessments

Time point	Screening and initial contact	Baseline	Randomisation	Group-based session	Post-session call	Follow-up
		Aim up to 14 days post-first contact		Weeks 1 to 5	Aim up to 6 weeks post-group-based session	3 months from post-randomisation (±3 weeks)
ENROLMENT						
Initial approach						
Informed consent						
Randomisation						
INTERVENTIONS						
Experimental (usual care plus JOINT SUPPORT)						
Control (usual care)						
ASSESSMENTS						
Screening logs						
Adverse event reporting						
Date of first appointment						
Patient age						
Patient gender						
Patient ethnicity						
Patient height						
Patient weight						
Patient medical history						
Patient occupational status						
Patient residential status						
Patient EQ-5D-5L						
Patient MSK-HQ						
Patient GSE						
Patient NRS pain						
Patient NRS fatigue						
Patient CES-D						
Patient Health Use Questionnaire						
Caregiver EQ-5D-5L						
Caregiver CES-D						
Caregiver Zarit Burden Questionnaire						
Caregiver Leisure Time Satisfaction Questionnaire						
Caregiver Health Use Questionnaire						
Caregiver age						
Caregiver gender						
Caregiver ethnicity						
Caregiver medical history						
Caregiver caregiving experience (duration/caregiver for another person)						
Caregiver residential status to patient						
Caregiver occupational status						
Working or not						
HCP usual care logs						
JOINT SUPPORT intervention logs						
Patient complications/adverse events						
Caregiver intervention home logs						
Caregiver acceptability intervention						
Patient–caregiver semi-structured interviews						
HCP semi-structured interviews						

CES-D, Centre for Epidemiologic Studies Depression Scale (CES-D); EQ-5D-5L, EQ-5D 5 level instrument; GSE, general self-efficacy scale; HCP, healthcare professional; MSK-HQ, Musculoskeletal Health Questionnaire; NRS, numerical rating scale.

To answer our feasibility objectives, we will assess:

Recruitment feasibility—by screening log data: number of potential patients and caregivers screened, assessed for eligibility; including reasons for exclusion/non-participation, and consented.Intervention acceptability—by conducting qualitative interviews with participants; recording study attrition at the intervention phase; analysing acceptability questionnaires for patients, caregivers and healthcare professionals.Intervention fidelity (healthcare professionals)—by analysis and reporting on intervention log checklist data on: intervention timing, duration, frequency, timing of intervention (during or after ‘active’ course of treatment); QA monitoring visit checklists; qualitative interviews.Intervention fidelity (caregivers)—by analysis and reporting on caregiver intervention logs; qualitative interviews.Randomisation acceptability—by analysis and reporting on screening logs, eligibility assessment logs and consent forms; participant attrition; qualitative interviews.Contamination risk—by analysis and reporting on intervention log data including: experimental and control intervention records; QA monitoring visit checklists; delegation logs; qualitative interviews (patient, caregiver and healthcare professional).

### Secondary outcomes

Outcome data completeness—by analysis and reporting on completion rates (baseline and 3 months post-randomisation) of: *Patient Participants*: Musculoskeletal-Health Questionnaire (MSK-HQ)^22^; numerical rating scale for pain and fatigue^23^; self-efficacy, assessed using the General Self-Efficacy Scale^24^; psychological distress (depression), assessed using the Centre for Epidemiologic Studies Depression Scale (CES-D)^25^; HRQoL assessed using the EQ-5D-5 level questionnaire (EQ-5D-5L)^26^; self-reported health resource use questionnaire; adverse events. *Caregiver Participants*: EQ-5D-5L^26^; CES-D^25^; the Zarit Burden Interview Scale—12-item version^27^; Leisure Time Satisfaction questionnaire^28^; self-reported health resource use questionnaire; adverse events.Signal of effectiveness—by calculating and reporting effect size measurement of the above outcome measures.

These measures were selected due to their robust psychometric properties and acceptable patient and caregiver burden as confirmed by our study patient representatives/clinician feedback. They reflect relevant core outcome sets including: lower limb osteoarthritis,^29^ low back pain^30^ and general musculoskeletal disease.^31^ Caregiver outcomes mirror the domains of importance reported through previous qualitative findings.^9^

Baseline assessment will be undertaken after patient and caregiver participants have signed the consent form, prior to randomisation. Patient and caregiver participants will be provided with a paper-based questionnaire to complete in their recruitment information pack. Baseline data collected will include: (for patient and caregiver): age, sex, ethnicity, occupational status (current or past if retired), medical comorbidities, presenting musculoskeletal pathology(ies); and for patient, duration of symptoms relationship of caregiver to patient; and for caregiver: duration of caregiving, whether caregiver for another person, whether lives with patient.

At 3 months post-randomisation, patient and caregiver participants will be sent a postal questionnaire. A 3-month follow-up period will provide an indication on follow-up completion and usability of the outcome instruments to answer a trial secondary outcome measure. Participants will be asked to complete and return this to the central trial team using a prepaid envelope. If participants do not return these questionnaires within 2 weeks of initial posting, the central trial team will telephone the participants (caregiver and/or care-recipient) to offer the option of completing the questionnaires over the telephone or to send a further questionnaire pack.

### Data analysis

#### Sample size

In total, 80 participant dyads (80 patients/80 caregivers) will be recruited. This sample size will be sufficient to answer our feasibility objectives and assess the a priori progression criteria (table 2).^32^ This number will also allow each site to test the JOINT SUPPORT programme in at least two complete cycles. This sample size follows recommendations^33^ for designing feasibility trials that aim to detect a small–medium standardised effect size (where the definitive trial will be designed with 80% power and two-sided 5% significance).^32 34^

**Table 2 T2:** Feasibility study stop–go, traffic light, progression criteria

	Green (go)	Amber (amend)	Red (stop)
Recruitment	>30% of the patients screened across the sites in 12 months would be eligible	20%–30% would be eligible	<20% would be eligible
Intervention fidelity (healthcare professionals)	>70% of the participant-dyads compliant with their allocated intervention (five face-to-face sessions and booster phone call) as randomised	50%–70% received intervention as randomised	<50% received intervention as randomised
Intervention fidelity (caregivers)	>90% of the participants adopted elements of JOINT SUPPORT programme post-last session	60%–90% adopted JOINT SUPPORT post-last session	<60% adopted elements post-last session
Randomisation acceptability	>40% of the eligible participants consent to be randomised	20%–40% would be randomised	<20% would be randomised
Contamination	<5% of the participants in either group received majority of their allocated treatment cross-over	5%–10% of the participants cross-over	>10% of the participants cross-over
Data collection completion	<15% missing outcome questionnaires for whatever reason at 3-month data collection	15%–30% missing questionnaires	>30% missing questionnaires

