#### Objectives

The main objectives are to assess the:

Feasibility of recruiting eligible patient and caregiver dyads in the NHS.Acceptability of the JOINT SUPPORT programme to caregivers, patients and healthcare professionals.Fidelity of delivery of the JOINT SUPPORT programme by healthcare professionals.Ability of caregivers to deliver components of the JOINT SUPPORT programme with fidelity, confidence and competency to patients at home.Acceptability of caregiving dyad randomisation for patients, caregivers and healthcare professionals.Risk of intervention contamination when experimental and control groups are delivered in the same setting.

The secondary objectives are to assess the:

Completeness of outcome measure data.Signal of the clinical effectiveness of the JOINT SUPPORT programme.

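### The professional-fidelity row of Table 2 describes a delivery mode and booster-call requirement that differ from the programme it scores, so its stop–go colour can depend on how the row is read

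*Protocol article*

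**What the plan says.** In the protocol article, Table 2 (under Sample size) has a row labelled as intervention fidelity of healthcare professionals. Its green cell reads ">70% of the participant-dyads compliant with their allocated intervention (five face-to-face sessions and booster phone call) as randomised". The amber cell reads "50%–70% received intervention as randomised" and the red cell "<50% received intervention as randomised". Neither repeats the bracketed definition.

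The programme being scored is described elsewhere:

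- **Mode.** The Experimental intervention section sets out two approaches. Under Approach 2, where an NHS organisation does not permit face-to-face consultations, "group-based video consultation sessions using an NHS authorised platform will be used to deliver the content of the JOINT SUPPORT programme". If service delivery changes after a dyad has started, "switching from Approach 1 to Approach 2 will be permitted".
- **Calls.** The section on telephone booster calls places them "during Week 1, 3 and 6 post-group session discharge", which makes three. The Abstract also gives three.
- **Objective and measurement.** A main objective is "Fidelity of delivery of the JOINT SUPPORT programme by healthcare professionals". The Assessment section plans to measure it as follows: "Intervention fidelity (healthcare professionals)—by analysis and reporting on intervention log checklist data on: intervention timing, duration, frequency", together with quality-assurance visit checklists and interviews. The Quality assessment section says that content, mode, frequency and deviations will be logged.

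The Progression criteria section makes the traffic lights a guide and sends unmet criteria to the trial oversight committee.

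**The concern.** The row is one of six a priori criteria that inform whether a definitive trial goes ahead. Its green definition disagrees with the intervention sections on two countable features.

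First, only face-to-face sessions count. A dyad treated by video as the protocol permits is non-compliant, and so is one that switched for a single session. Second, the call is in the singular where the programme has three, so a dyad that received one or two calls can be scored compliant.

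The label adds a further difficulty. The row counts dyads that complied with or received the programme. Nothing in it reflects whether the therapist covered the content of each session, although the logs and visit checklists record that. A therapist who leaves out material can contribute to green, and a faithful therapist whose dyad misses a session contributes a failure.

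If the definition is settled only after the data are seen, the colour is partly chosen and no longer pre-specified.

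**Working it through.** The 70% and 50% cut-points are set values with no derivation behind them, so there is no stated figure to reproduce. The check applies the row under each reading. The article gives no expected video share, session completion or call reach, so *c*, *v*, *s* and *p* below are all assumptions.

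**Delivery mode.** Let *c* be the proportion of JOINT SUPPORT dyads receiving the full programme by either approach, and *v* the share treated by video, taken as unrelated to receipt.

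- Literal rate = c × (1 − v).
- Green is lost when v exceeds 1 − 0.70/c, and red is reached when v exceeds 1 − 0.50/c.

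| c | green lost above | red above |
|---|---|---|
| 75% | 6.7% | 33.3% |
| 85% | 1 − 0.70/0.85 = 17.6% | 1 − 0.50/0.85 = 41.2% |
| 100% | 30% | 50% |

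At c = 85%, counting both modes gives 85% (green). Counting face-to-face only gives 0.85 × 0.80 = 68% (amber) at v = 20%, and 0.85 × 0.50 = 42.5% (red) at v = 50%.

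Sampling variation was added with exact binomial probabilities. The JOINT SUPPORT arm is taken as 53 dyads (80 × 2/3, if the stated 2:1 favours it) or 40 (if allocation is equal). Green then needs at least 38 of 53 or 29 of 40, and red is at most 26 of 53 or 19 of 40.

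| c = 85%, video share | n = 53 | n = 40 |
|---|---|---|
| 0% | P(green) 0.996 | P(green) 0.988 |
| 20% | P(green) 0.339 | P(green) 0.336 |
| 50% | P(red) 0.865 | P(red) 0.789 |

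**Booster calls.** Let *s* be the proportion completing the five sessions and *p* the chance that each of the three calls takes place, unrelated to *s*.

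- At least one call, independent calls: s × (1 − (1 − p)³).
- All three calls, independent calls: s × p³.
- Fully dependent calls (all or none): both readings equal s × p, which is also the ceiling for all three.

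| s = 85% | at least one, independent | all three, independent | either reading, fully dependent |
|---|---|---|---|
| p = 80% | 0.85 × 0.992 = 84.3% (green) | 0.85 × 0.512 = 43.5% (red) | 68% (amber) |
| p = 90% | 0.85 × 0.999 = 84.9% (green) | 0.85 × 0.729 = 62.0% (amber) | 76.5% (green) |

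At p = 80%, between these extremes of dependence, the all-three rate runs from 43.5% to 68%. It never reaches green.

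**Both together.** The face-to-face reading lowers the score and the single-call reading raises it. Take s = 85%, p = 80%, independent calls and 20% video. The literal row gives 0.80 × 84.3% = 67.5% (amber). Counting both modes and all three calls gives 43.5% (red). The two discrepancies do not cancel here.

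**The case against.** **The singular may be loose wording.** The cell does not say one call, and the phrase may only name the call component. This stands in part. The row cannot be said to require exactly one call, but as written it does not require three.

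**Video may not occur.** Approach 2 applies only where face-to-face contact is not permitted, and the amber and red cells use wording that a video dyad satisfies. Both points are fair. The first makes the effect conditional. The second shows that the three cells do not share a definition, which is itself a reason to reword them.

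**Some video use is compatible with green.** The interview targets imply four sites (two professionals per site, eight in total). With one of four equal sites on video the ceiling is 75%, so green is still reachable, though it needs more than 0.70/0.75 = 93% receipt at the other three. With two sites on video the ceiling is 50%, which is amber. A reader might infer that permitted video use alone forces a stop. With full receipt it does not at these shares.

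**Receipt is part of fidelity.** The Assessment section includes session frequency in professional fidelity, so receipt of sessions and calls is a narrow dose summary. Content is captured elsewhere, and the Analysis section reports fidelity with 95% confidence intervals. This stands. A reader might conclude that the row measures something unrelated to delivery, which goes too far. It measures one component under a label that promises more.

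**The oversight committee can correct it.** Unmet criteria are discussed, and delivery mode is logged, so a false amber or red would probably be recognised. The stated process does not call for discussion of a criterion that is met, so it gives less protection against a false green.

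A reader might also infer that usual-care dyads enter the count because the cell refers to the allocated intervention. The bracket defines that intervention as the sessions and call, which only JOINT SUPPORT dyads can receive. Any calculation of such dilution would also need the direction of the 2:1 ratio, which the randomisation section does not give, while the professional interview guide (Table 4) speaks of 50% not receiving the programme.

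**Conclusion.** The point holds as an inconsistency between one progression criterion and the intervention it scores, on delivery mode and on booster calls, with a label broader than what the row counts. The mismatches are in the text and need no assumption.

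Their effect on the colour is conditional. It depends on Approach 2 being used, on calls being missed, and on how far missed calls cluster within dyads: with full clustering the call discrepancy makes no difference. Under the assumed rates the mode discrepancy can turn a comfortable green into amber or red, and the call discrepancy can turn red or amber into green. The documents do not support saying that the row will give the wrong colour, or in which direction the net error would fall.

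This is a wording correction to a decision rule. It is worth making before the data are examined because it costs little and settles the definition in advance.

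**What to change.** Reconcile the Table 2 row with the Approach 1 and 2 text and the booster-call section. Then:

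1. State the denominator as dyads randomised to JOINT SUPPORT.
2. Count receipt of the five group sessions by either permitted approach, and of the booster calls as the reconciled text specifies them.
3. Use that same definition in the green, amber and red cells.
4. Label the row as dyad receipt or adherence.
5. Report professional content fidelity beside it, from the intervention logs and visit checklists already planned, for the oversight committee to read together with the colour.

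There is no need to turn content fidelity into a further traffic light scored per session. That would change the unit from dyads to sessions, and the 70% and 50% cut-points have no stated basis on that scale.

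The cost is a change of table wording and one tabulation of data already collected. The adherence figure may look slightly less favourable.

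### The healthcare-professional fidelity criterion in Table 2 counts only face-to-face sessions, although video delivery is permitted, and does not say how many of the three booster calls are required

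*Protocol article*

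**What the plan says.** Table 2 (Protocol article, Data analysis, Sample size) sets the stop–go bands for healthcare-professional fidelity. The green cell requires more than 70% of dyads to be "compliant with their allocated intervention (five face-to-face sessions and booster phone call) as randomised". The amber cell reads "50%–70% received intervention as randomised" and the red cell "<50% received intervention as randomised". Neither repeats the definition in the green cell.

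The description of the experimental intervention gives two routes. Approach 1 is face-to-face. The second is conditional: "Approach 2: Video consultation if face-to-face consultations are not permitted within a participating NHS organisation". In that case, "group-based video consultation sessions using an NHS authorised platform will be used to deliver the content of the JOINT SUPPORT programme". If service delivery changes after a dyad has started, "switching from Approach 1 to Approach 2 will be permitted". The section on the training programme defines session length without regard to mode: "Irrespective of delivery method, each session will be up to 60 min".

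On calls, the section on telephone boosters says that a healthcare professional "will telephone each caregiver and patient as a dyad during Week 1, 3 and 6 post-group session discharge", which makes three calls. The abstract also gives three.

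**The concern.** Fidelity of delivery by healthcare professionals is one of the main objectives, and this row is its progression criterion. The intervention section uses face-to-face as the opposite of video, so the term in Table 2 cannot easily be read as covering both. A site that moves to video as the protocol allows would then lower its fidelity score without delivering the programme any less faithfully.

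The call requirement is a separate weakness. The row mentions a booster call without a number, while the programme has three. Someone scoring the row could ask for at least one call or for all three, and the choice can change the colour.

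Because only the green cell carries a definition, a video dyad could also fail the green wording and yet satisfy the amber wording. The Sample size section presents these criteria as set in advance. If the definition is settled only once the data are in, that no longer holds for this row.

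**Working it through.** The plan states no figure that depends on this definition, so there is nothing to reproduce. The check has two parts. In both, the denominator is taken to be the JOINT SUPPORT dyads, because the definition lists only components of that programme.

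**1. Delivery mode**

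Inputs from Table 2: green above 70%, amber 50% to 70%, red below 50%. Input not in the documents: the share *v* of dyads with at least one video session.

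If a fraction *d* of dyads complete the programme, whatever their mode, the literal score is *d* × (1 − *v*).

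- Perfect delivery (*d* = 1): the score is 1 − *v*. At *v* = 0.30 it is 0.70, which is not above 70%, so green is ruled out from there on. For *v* above 0.50 the score is below 50%, which is red. If mode is ignored, the same trial scores 100%.
- Illustration with an assumed *d* = 0.85: at *v* = 0.25, 0.85 × 0.75 = 63.8% (amber); at *v* = 0.50, 0.85 × 0.50 = 42.5% (red); at *v* = 0, 85% (green).

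In numbers of dyads, under perfect delivery:

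| JOINT SUPPORT dyads | Green needs | Video dyads that rule out green | Video dyads that force red |
|---|---|---|---|
| 53 (80 split about 2:1, larger arm assumed experimental) | 38 (38/53 = 71.7%) | 16 (37/53 = 69.8%) | 27 (26/53 = 49.1%) |
| 40 (80 split 1:1, as the healthcare-professional interview guide implies) | 29 (29/40 = 72.5%) | 12 (28/40 = 70.0%) | 21 (19/40 = 47.5%) |

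Approach 2 depends on what an organisation permits, so video would tend to arrive a whole site at a time. The Qualitative study section implies four sites (two professionals per site, eight in total). If the four recruited equally, which is an assumption, one site wholly on video would cap the literal score at 75%. Green would then need more than 0.70 / 0.75 = 93.3% completion at the other three.

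**2. Number of calls**

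Assume that each contact is attended independently with probability *a*. Neither the independence nor the value of *a* comes from the documents.

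- Lenient reading, five sessions and at least one of three calls: *a*⁵ × [1 − (1 − *a*)³].
- Strict reading, five sessions and all three calls: *a*⁸.

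| *a* | Lenient | Strict |
|---|---|---|
| 0.85 | 44.2% (red) | 27.2% (red) |
| 0.90 | 59.0% (amber) | 43.0% (red) |
| 0.92 | 65.9% (amber) | 51.3% (amber) |
| 0.95 | 77.4% (green) | 66.3% (amber) |
| 0.96 | 81.5% (green) | 72.1% (green) |

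The lenient score reaches 50% at *a* = 0.871 and 70% at *a* = 0.931. The strict score reaches them at *a* = 0.917 and *a* = 0.956. The two readings therefore give different colours only for attendance of about 87% to 92% and about 93% to 96%, and the same colour elsewhere.

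**The case against.** The strongest reply has four parts.

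- **Video is a contingency.** It applies only where face-to-face is not permitted or service delivery changes. No passage makes a large share likely, and with no video sessions the mode conflict costs nothing. This stands and limits the size of the point. It does not remove the conflict, because the protocol plans for the contingency and the row does not.
- **The traffic lights are a guide.** Under Progression criteria, the trial oversight committee discusses unmet criteria and may proceed with or without refinements. Mode and deviations are logged (Quality assessment), so a low score caused by video would be visible. This stands and lowers the severity. But the committee would then be choosing the definition after seeing the data.
- **The call wording may be shorthand.** Table 2 gives no number, so it does not state a count that contradicts three. This stands: the wording is under-specified.
- **The full protocol may hold an operational definition.** That would excuse silence. On mode, however, the article is not silent: it states a definition that conflicts with its own intervention description.

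A reader might infer more, namely that dyads treated exactly as planned generally score as non-compliant. The documents do not support that. A dyad treated wholly face-to-face is unaffected. A dyad that receives all three calls has received a booster call and meets the wording; if the call wording errs, it errs towards leniency, since a dyad with one call may count too. Nor does the protocol present video as a route equal to face-to-face.

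**Conclusion.** The point holds for dyads with at least one permitted video session: read as written, the row scores them as non-compliant. With perfect delivery, a video share of 30% or more rules out green and a share above 50% gives red. These limits follow from Table 2's own cut-offs. How likely they are to be reached cannot be judged, because the documents give no video share.

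The number of calls required is left open. Under independent attendance the choice of reading moves the row by one colour over part of the plausible range (about 87% to 92% and 93% to 96% per contact) and has no effect on colour outside it.

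This should be fixed but is not critical. It affects a pre-set criterion for a main objective, while the committee's review offers some protection. The sample size of 80 dyads and the clinical outcome estimates do not depend on it.

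**What to change.** Reconcile the Table 2 row with the sections on delivery approaches, training sessions and booster calls:

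- count a session delivered in either permitted mode towards the five;
- state how many of the three planned calls the compliance count uses;
- apply that one definition to the green, amber and red cells.

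This is a rule for counting and changes nothing in how dyads are treated. The cost is rewording one table row before the criterion is scored. No new data are needed, since the Quality assessment section already has mode of delivery and frequency recorded in the intervention logs. Reporting the rate separately for face-to-face, video and switched dyads would help the committee but is optional.
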